##### Stage C

##### Stage C-1 and C-1b

- Primary objective:  
To evaluate the safety of the two leprosy skin test antigens in small numbers of healthy contacts of leprosy patients, BT/TT leprosy patients, BL/LL leprosy patients, and TB patients.

- Secondary objectives:
  - To evaluate responses to the two leprosy skin test antigens and to PPD/tuberculin in healthy contacts of leprosy patients, BT/TT leprosy patients, BL/LL leprosy patients, and tuberculosis patients to determine if these leprosy antigens show promise for the selective diagnosis of leprosy infection.
  - To apply a whole blood assay for IFN- $\gamma$  response to these antigens, and an antibody response to the leprosy specific PGL-I antigen, to these population groups, in order to provide preliminary indications as to *in vivo* skin testing being replaced or augmented with blood assays.

## 13.2 Study Population

All subjects for Stages A, B, and C will be Nepali nationals (including expatriates from India), between the ages of 18 and 60 years, weighing greater than 30 Kg (female) or 38 Kg (male). Healthy, non-leprosy exposed subjects and tuberculosis patients will serve as the negative control group. Healthy leprosy exposed contacts and BT/TT leprosy patients will serve as positive control groups, and BL/LL leprosy patients will serve as concurrent controls.

The skin test reactions will vary among the groups participating in this study. It is expected that the non-contacts and BL/LL leprosy cases along with the tuberculosis patients will have smaller or negative indurations at all leprosy skin test sites. The tuberculosis patients will react with a large induration at the PPD/tuberculin site, and may react with an induration less than 10 mm at the other sites. Healthy contacts of leprosy patients and BT/TT leprosy patients are expected to have larger indurations at *M. leprae*-derived antigen sites, and a variable reaction at the site of the PPD/Tuberculin. Data collected from skin test reactions from these five groups will allow study objectives to be met.

The rationale for choosing these study groups is as follows. Healthy subjects not exposed to leprosy will be considered endemic area controls, which are necessary to monitor exposure to environmental mycobacteria and/or exposure to tuberculosis. This group of volunteers will be recruited to establish the safety of both antigens and antigen dosages, as well as to establish a baseline response in a leprosy endemic area. Tuberculosis patients will serve as controls recruited to aid in establishing the specificity of leprosy skin test antigens and to show PPD positivity. The healthy contact group (including family members of leprosy patients) will serve as a positive response group. That is, in comparison to the proportion of healthy non-contacts with a positive reaction to the test antigens, we expect that at least twice as many healthy contacts of leprosy patients will have a positive test, due to the fact that the contacts have been exposed to leprosy and probably have developed at least a small immunological reaction to *M. leprae*. On the other hand, the leprosy patient study groups (BT/TT and BL/LL) fall into two categories at opposite ends of the disease spectrum. Historically, BT/TT leprosy patients produce a strong skin test response against leprosy antigens, because of their strong T-cell response to *M. leprae*. In comparison, BL/LL leprosy patients produce a weak or negligible response due to an anergic T-cell response to leprosy skin test

antigens. Alternatively, the B-cell immunological response is weak in BT/TT leprosy patients and strong in BL/LL leprosy patients. Data collected from each group will be analyzed by comparing the mean skin test response against leprosy skin test antigens as compared to PPD, thus enabling questions of safety and specificity to be addressed.

Ethical concerns have been taken into account for each group of volunteers. It is expected that healthy non-contacts, tuberculosis patients, and some BL/LL patients may have small (less than 10mm) induration reactions to the leprosy skin test antigens, due to cross-reactivity with *M. tuberculosis*, BCG vaccination, and/or environmental mycobacteria. Known environmental mycobacteria present in soil and water include: *M. avium-intracellulare*, *M. kansasii*, *M. xenopi*, *M. ulcerans*, *M. marinum*, *M. malmoense*, *M. fortuitum*, and *M. chelonae*. Tuberculosis patients are expected to produce a strong induration (10-30mm) response to PPD, however, the reaction is not expected to develop into an AE based on previous PPD testing in this region. Since tuberculosis is prevalent in Nepal and many individuals were vaccinated with BCG, most subjects will have been exposed to tuberculosis antigens, and therefore the remaining groups (healthy non-contacts, BL/LL and BT/TT leprosy patients, and contacts of leprosy patients) may react to PPD. Hence, PPD testing will be a measure of not only exposure to tuberculosis, but also BCG vaccination, and/or non-pathogenic environmental mycobacteria, to some extent. Finally, BT/TT leprosy patients and healthy contacts of leprosy patients are expected to respond more strongly (greater than 10mm induration) to leprosy skin test antigens. In order to minimize the risk to these groups, a preliminary test of each antigen at the high dose (1.0µg/100µl) will be tested in a small group of 20 subjects from each group, except the healthy non-contacts (Stage C-1). If serious adverse events are indicated, the causative antigen or antigen dose will be dropped from the study, following a safety review. To provide a comparative population at the low dose (0.1µg/100µl), Stage C-1b will be performed. Overall, the anticipated risks are the same as those encountered with other intradermal antigens such as tuberculin (see Section 2.3.1.1, "Skin Testing Risks").

### 13.3 Study Design

This is a prospective study where the participants all receive the same set of antigens, but are randomized to receive them in different patterns, that is, according to different “templates”. The participants do not know which template is used and the readers, or evaluators are also blinded to the pattern of antigen delivery. Stages A and B randomized participants to only a single study antigen, at two doses for each volunteer, plus PPD and saline. Schemas for stages A plus B and C follow.

[figure not shown]

Volunteers in stage C-1 will receive both leprosy skin test antigens at the high dose of 1µg per 100µl and PPD at 2TU, while volunteers from stage C-1b will receive the same antigens at the low dose of 0.1µg per 100µl and PPD at 2TU. Since three test sites are required as compared to four in Stage A and B, they will be reassigned (2 sites on the first arm and one on the second arm), and administration templates will be randomized to different administration patterns. For Stage C-1 and C-1b, there will be 20 subjects from each study group, except healthy non-contacts (contacts of leprosy patients; BT/TT and BL/LL leprosy patients; and, tuberculosis patients).

[figure not shown]

### 13.4 Study Outcome Measures

The primary outcome measure of this study is induration resulting from the skin test antigen DTH response. The method for measuring induration has been described in Section 4.5, "Methods for Collecting Data for Assessment of Study Objectives". As mentioned previously, evaluation of this observation variable will be performed using the same techniques used to evaluate the tuberculin/PPD response. A tuberculin reaction greater than 10mm of induration is classified as positive for persons who are not immunocompromised or previously in contact with TB patients, but have other risk factors for TB, such as living in a country where TB is prevalent. Induration measurements will be taken on days 2 and 3 (Stage A) and days 3 and 7 (Stage B and C) after skin test administration, at each test antigen site. If a subject is observed to have an induration greater than 10 mm at any injection site, at either study visit, they will

be asked to return at 25-31 days for a final induration measurement. Any reaction that persists will be followed-up until resolved or stabilized.

### 13.5 Study Hypotheses

This study is not designed to test a formal hypothesis such as the superiority or non-inferiority of different interventions. Rather, it is designed to describe the safety and primary response measure of induration resulting from skin test antigen DTH responses in selected groups all living in the same environment where leprosy is endemic.

An informal statement of the safety hypothesis for this study is that the study antigens are safe in all five-study groups. The study hypothesis for the diagnostic DTH response is that induration responses will be distributed in an approximately bi-modal fashion such that the healthy contacts of leprosy patients and BT/TT leprosy patients have generally larger responses in comparison to the other groups. If such a bi-modal distribution is observed for either antigen, it will be used to define positive responses, response rates for the different groups, sensitivity and specificity of the response, and the performance of the two antigens will be compared.

### 13.6 Sample Size Considerations

The primary variable outcome measure used for all calculations will be the mean induration measurement obtained from two independent readers for each skin test site. Our experience in this region of Nepal suggests that no more than 10% of subjects will be lost to follow-up. We are not planning to administer skin tests to additional subjects should some of the subjects not return for the 45-51 hour or later readings.

#### 13.6.1 Safety

Stage C-1 and C1b are intended to provide safety information on small numbers of participants (N=20 for each stage) within each of four different groups that theoretically may be at higher risk of serious adverse responses to the novel antigens. The table below shows the probability of observing 1 or more serious adverse events up to 5 or more serious adverse events, related to antigen administration. This probability is calculated from a sample of 18 subjects (20 subjects minus the possible loss of 10%) for a range of assumed "true" but unknown probabilities of a serious adverse event. Based on these results, if the true serious adverse event rate is 10% then there is an 85% chance of observing one or more serious adverse events in any one of the four groups, even if there is a 10% loss to follow-up within groups. Additional calculations, not shown, demonstrate that when there is no loss to follow-up the chance of observing at least one event increases to 88%. Aggregating the four groups and assuming 10% loss (n=72) there would still be an 89% probability of observing at least one event assuming that the groups in aggregate had a true event rate as low as 3%.

**Probability of Observing Adverse Events Within Any Study Group in Parts C-1 and C-1b Given a Range of True but Unknown Event Probabilities**

*Sample Size of 18 (assuming 2 lost to follow-up)*

| "True" Unknown Population Probability of an Event | Probability of Observing 1 or more Events | Probability of Observing 2 or more Events | Probability of Observing 3 or more Events | Probability of Observing 4 or more Events | Probability of Observing 5 or more Events |
|---------------------------------------------------|-------------------------------------------|-------------------------------------------|-------------------------------------------|-------------------------------------------|-------------------------------------------|
| -0.10%                                            | 1.78%                                     | 0.02%                                     | 0.00%                                     | 0.00%                                     | 0.00%                                     |
| 0.50%                                             | 8.63%                                     | 0.36%                                     | 0.01%                                     | 0.00%                                     | 0.00%                                     |
| 1.00%                                             | 16.55%                                    | 1.38%                                     | 0.07%                                     | 0.00%                                     | 0.00%                                     |
| 2.00%                                             | 30.49%                                    | 4.95%                                     | 0.52%                                     | 0.04%                                     | 0.00%                                     |
| 3.00%                                             | 42.20%                                    | 10.03%                                    | 1.57%                                     | 0.18%                                     | 0.02%                                     |
| 4.00%                                             | 52.04%                                    | 16.07%                                    | 3.33%                                     | 0.50%                                     | 0.06%                                     |
| 5.00%                                             | 60.28%                                    | 22.65%                                    | 5.81%                                     | 1.09%                                     | 0.15%                                     |
| 10.00%                                            | 84.99%                                    | 54.97%                                    | 26.62%                                    | 9.82%                                     | 2.82%                                     |
| 15.00%                                            | 94.64%                                    | 77.59%                                    | 52.03%                                    | 27.98%                                    | 12.06%                                    |
| 20.00%                                            | 98.20%                                    | 90.09%                                    | 72.87%                                    | 49.90%                                    | 28.36%                                    |
| 25.00%                                            | 99.44%                                    | 96.05%                                    | 86.47%                                    | 69.43%                                    | 48.13%                                    |

As the above table shows, the probability of observing events of a given underlying 'true' probability is identically in C-1 and C-1b since the sample sizes of the two parts are the same. If the 'true' probability of an event is similar in both groups, then combining parts C-1 and C-1b may provide further precision in the estimation of the probability of observing the indicated number of events. In particular, if the true serious adverse event rate is 10% then there is more than a 97% chance of observing one or more serious adverse events in any one of the four groups, even if there is a 10% loss to follow-up within groups.

**Probability of Observing Adverse Events Within Any Study Group when  
Combining Parts C-1 and C-1b Given a Range of True but Unknown Event  
Probabilities**

*Sample Size of 36 (assuming 4 lost to follow-up)*

| "True"
Unknown
Population
Probability of
an Event | Probability of
Observing
1 or more
Events | Probability of
Observing
2 or more
Events | Probability of
Observing
3 or more
Events | Probability of
Observing
4 or more
Events | Probability of
Observing
5 or more
Events |
|---------------------------------------------------------------|----------------------------------------------------|----------------------------------------------------|----------------------------------------------------|----------------------------------------------------|----------------------------------------------------|
| 0.10%                                                         | 3.54%                                              | 0.06%                                              | 0.00%                                              | 0.00%                                              | 0.00%                                              |
| 0.50%                                                         | 16.51%                                             | 1.41%                                              | 0.08%                                              | 0.00%                                              | 0.00%                                              |
| 1%                                                            | 30.36%                                             | 5.03%                                              | 0.56%                                              | 0.05%                                              | 0.00%                                              |
| 2%                                                            | 51.68%                                             | 16.18%                                             | 3.50%                                              | 0.57%                                              | 0.07%                                              |
| 3%                                                            | 66.60%                                             | 29.41%                                             | 9.28%                                              | 2.22%                                              | 0.42%                                              |
| 4%                                                            | 77.00%                                             | 42.50%                                             | 17.34%                                             | 5.46%                                              | 1.37%                                              |
| 5%                                                            | 84.22%                                             | 54.33%                                             | 26.79%                                             | 10.37%                                             | 3.24%                                              |
| 10%                                                           | 97.75%                                             | 88.74%                                             | 71.21%                                             | 49.15%                                             | 28.92%                                             |
| 15%                                                           | 99.71%                                             | 97.88%                                             | 92.24%                                             | 80.94%                                             | 64.50%                                             |
| 20%                                                           | 99.97%                                             | 99.68%                                             | 98.40%                                             | 94.78%                                             | 87.31%                                             |
| 25%                                                           | 100.00%                                            | 99.96%                                             | 99.74%                                             | 98.90%                                             | 96.58%                                             |

As described in the above table, Stage C-1b provides increased probability of detecting safety concerns. In addition, combining BT/TT and BL/LL leprosy groups and the contact groups from C-1 and C-1b provides a cumulative sample of 108 assuming a 10% loss. Considering this combined group, there will be better than 91% probability of observing at least one event with a true incidence rate of the event is 2% or higher.

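### The chance of seeing a 2% event in the 108 pooled leprosy and contact subjects is 88.7%, not better than 91%; 91% needs all 120 with no loss

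*Protocol*

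**What the plan says.** Protocol section 13.6.1 supports the safety sample size of Stages C-1 and C-1b with the probability of observing at least one event for a range of true event rates. It tabulates this for one group in one stage (20 enrolled, 18 after loss) and for one group over both stages (40 enrolled, 36 after loss).

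After the second table it takes a larger pool, "combining BT/TT and BL/LL leprosy groups and the contact groups from C-1 and C-1b", and says that this "provides a cumulative sample of 108 assuming a 10% loss". The next sentence refers back to that pool and says that "there will be better than 91% probability of observing at least one event" "with a true incidence rate of the event is 2% or higher".

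The components of the 108 are given elsewhere. Section 13.3 says: "For Stage C-1 and C-1b, there will be 20 subjects from each study group, except healthy non-contacts". Section 13.6 expects that "no more than 10% of subjects will be lost to follow-up".

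**The concern.** The probability and the sample size in these adjoining sentences do not belong together. For a rate of 2% or higher, the chance of seeing at least one event is lowest at exactly 2%, so a claim of better than 91% has to hold there. With 108 subjects it does not.

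Safety is the first-listed primary objective in section 3.1 and the only primary objective of Stages C-1 and C-1b in section 13.1.2. The sentence closes the safety sample-size argument, directly after the remark that Stage C-1b improves the chance of detecting safety problems. It is also the only figure in the section that pools the three leprosy-related groups over both stages. A safety committee or ethics board that relies on it would take the detection probability to be somewhat better than it is, and would believe that the allowance for loss had already been made.

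**Working it through.** **Inputs**

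- Groups pooled: BT/TT, BL/LL and contacts, 3 groups (13.6.1).
- Stages pooled: C-1 and C-1b, 2 stages (13.6.1).
- Subjects per group per stage: 20 (13.3).
- Loss to follow-up: 10% (13.6).
- True event rate: 2%, the lower end of the stated range (13.6.1).

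**Sample size**

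3 × 2 × 20 = 120 enrolled, and 120 × 0.9 = 108 after loss. The protocol's 108 is correct.

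**Formula**

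For n independent subjects with event probability p, P(at least one event) = 1 − (1 − p)^n.

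**Check that this is the protocol's method**

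| Case in 13.6.1 | n | p | Recomputed | Stated |
|---|---|---|---|---|
| One group, one stage, after loss | 18 | 10% | 84.99% | 84.99% (85% in the text) |
| One group, one stage, no loss | 20 | 10% | 87.84% | 88% |
| Four groups, one stage, after loss | 72 | 3% | 88.84% | 89% |
| One group, both stages, after loss | 36 | 2% | 51.68% | 51.68% |
| One group, both stages, after loss | 36 | 10% | 97.75% | 97.75% (more than 97% in the text) |

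All 110 cells of the two tables (11 rates × 5 event counts × 2 sample sizes) also agree with the exact binomial to the two decimals printed, reading the first rate of the first table, printed with a minus sign, as 0.10%. The method is therefore not in doubt.

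**The disputed figure**

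- n = 108, p = 2%: 1 − 0.98^108 = 1 − 0.1128 = 0.8872, or 88.7%.
- n = 119, p = 2%: 1 − 0.98^119 = 0.9097, just short of 91%.
- n = 120, p = 2%: 1 − 0.98^120 = 1 − 0.0885 = 0.9115, the first sample size above 91%.

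Solving for n gives the same answer: ln(0.09) / ln(0.98) = 119.2, so 120 subjects are needed. With n fixed at 108, 91% is reached at p = 1 − 0.09^(1/108) = 2.20%.

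**Other readings tried**

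- Poisson approximation at n = 108: 1 − exp(−2.16) = 88.5%.
- All four groups, both stages, after loss (n = 144): 94.5%.
- All four groups, both stages, no loss (n = 160): 96.1%.

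None of these gives a figure just above 91%.

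**Size of the gap**

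- Detection: 91 − 88.7 = 2.3 points.
- Chance of missing a 2% event: 11.3% against an implied 9% or less, a ratio of 11.3 / 9 = 1.25.

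**The case against.** The arithmetic cannot be contested, but four points can fairly be made about its weight.

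First, the 10% loss is a ceiling, and section 13.9.1 itself calls the allowance generous. On the protocol's own assumptions the pooled sample lies between 108 and 120, and the probability between 88.7% and 91.15%. In addition, section 8.3.1 has every subject examined about 15 minutes after injection, so later loss hardly affects the detection of immediate reactions. This narrows the practical gap. It does not make the sentence true, because the sentence is about the 108.

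Second, nothing depends on the number. Section 13.5 disclaims formal hypothesis testing, section 13.8.4 has no statistical halting rule, and section 11.4 suspends enrolment on individual events. The 20 per group is nowhere derived from the 91%. This stands, and it limits the consequence to a misdescribed property.

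Third, the gap is small in absolute terms, and the 25% relative increase in the chance of a miss makes it look larger than 2.3 points. That is fair; both figures describe the same gap.

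Fourth, that the 91% came from n = 120 is an inference from the numerical match. The protocol does not say so. The mismatch itself needs no such inference.

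**Conclusion.** The sentence is wrong as written. The 108 subjects it names give an 88.7% chance of at least one event at a true rate of 2%; better than 91% requires the full 120. The result uses only the protocol's own sample size and rate. It assumes independent subjects with a common event probability, as the rest of section 13.6.1 does.

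The common probability deserves a remark, since the pool combines subjects given 1.0 µg (C-1) with subjects given 0.1 µg (C-1b). Section 13.6.1 makes pooling of the two stages conditional on similar event probabilities when it introduces the n = 36 table, but does not repeat the condition here. Within one stage the same three groups give 3 × 18 = 54 subjects after loss, and 1 − 0.98^54 = 66.4%. The arithmetic finding does not depend on this.

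The error overstates a descriptive safety property by about 2.3 points and leaves the sample size, the analyses and the conduct of the trial unchanged. It should be corrected because the stated sample does not deliver the stated probability.

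**What to change.** In the last sentence of section 13.6.1, replace the 91% with about 89% (88.7%) at a true rate of 2% for the 108 subjects. Alternatively, keep 91% and attach it expressly to 120 subjects with no loss to follow-up, preferably beside the after-loss figure, as the section already does for a single group (85% and 88%).

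Optionally, repeat there that pooling C-1 with C-1b assumes similar event rates at the two doses, and give the per-stage figure of 66% (n = 54).

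The cost is one corrected sentence, with no change to design, sample size or analysis.
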